5.1　Efficacy endpoints

The following efficacy evaluations are for single dosing. If additional treatment (one time) is given, the results are evaluated 3 months after the additional dose (1 month after the additional dose for “5.1.2.2 Other secondary endpoint” #2), compared with the results before the first dose.

The calculation (evaluation) of the volume of venous malformations for the primary and secondary endpoints will be performed by the Central Judgment Committee independent from the Coordinating Committee, the investigator and the subinvestigator, based on the calculation method determined in advance by the Committee on Methods of Calculating Lesion Volume. Details of the Central Judgment Committee are separately stipulated in the "Procedures for the Central Judgment Committee.

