4.1.10　Additional treatment

For patients with diffuse lesions (when the target lesion is a diffuse lesion), and there is little improvement in symptoms such as pain after 4 weeks from the initial treatment (when there is almost no change in VAS [Visual Analogue Scale] or when an exacerbation is observed), and the investigator or subinvestigator determines that additional treatment is necessary, additional treatment may be performed once within 3 months (whether or not additional treatment is necessary is determined at least 4 weeks after the initial treatment). The dosage and administration of the additional treatment should be the same as that of the initial treatment. If additional treatment is conducted, the efficacy and safety is evaluated 3 months after the additional treatment.

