4.1.11　Duration of a drug administration

Single dose. However, if the target lesion is a diffuse lesion, additional treatment may be performed once if necessary.

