5.1.1　Primary endpoint

Achievement of at least 20% reduction in volume of venous malformations from baseline (prior to administration) at 3 months of treatment with the investigational drug

[Basis for setting up].

Validity of the evaluation items:

In an ongoing Japanese investigator-initiated clinical trial of oral sirolimus treatment for lymphatic malformations, which is a similar disease of venous malformations, a 20% or greater reduction in the volume of the target lesion on MRI is considered a partial response (PR). Since the presence of a lesion can cause various symptoms, a reduction in volume of 20% or more is clinically significant. In addition, many literature studies have shown that patients with lesion reduction also experience improvement in pain.

In a trial conducted in the U.S. for oral sirolimus treatment of refractory vascular malformations, one of the endpoints was a 20% or greater reduction in the volume of the target lesion by MRI as PR, and the above domestic trial is based on this evaluation standard.

Validity of the evaluation period:

In evaluating the efficacy of sclerotherapy with monoethanolamine oleate, previous reports include Kaji et al.^5)^ evaluated by MRI at 3 months after treatment; Hoque et al.^6)^ evaluated at 8 weeks after sclerotherapy. A trial of gastric varices with a similar mechanism evaluated at 90 days after treatment. Based on these previous reports, the evaluation period was set at 3 months.

Regarding safety, Nomura et al. reported^9)^ that skin necrosis or mucous membrane necrosis was observed in 14.7% of patients, but all of them improved with conservative treatment. The average time required for healing was 58.6 days (maximum approximately 90 days). Generally, the adverse drug reactions by sclerotherapy occur within a few days of treatment, and considering the period until the adverse drug reactions are cured as the necessary observation period, it is reasonable to set the evaluation period at 3 months.

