| pain | VAS |  |  |  |  | X | X | X |  |
|  | Face scale | X | X | X | X |  |  |  |  |

12) At "pre-dose (screening)", "1 day before administration", and "3 months after administration (12 weeks after administration)", two assessments of pain are performed: "last 24 hours" and "last 1 week" (other visits are only "last 24 hours").

13) In patients with diffuse lesions, if there is lack of improvement in pain after 4 weeks from the initial treatment and the investigator or subinvestigator determines that it is therapeutically necessary, an additional treatment (one time) may be administered within 3 months (whether or not additional treatment is necessary is determined at least 4 weeks after the initial treatment). The dosage and administration of the additional treatment should be the same as that of the initial treatment.

14) Additional CT scan or ultrasound may be performed as needed.

15) For MRI imaging only, the acceptable range after 3 months of administration is ±14 days.

16) For the QOL evaluation scales, the EQ-5D Japanese version is used for patients aged 15 years and older, and the PedsQL Japanese version for patients aged 5 to 14 years. however, evaluation for children aged 5 years is not mandatory. For guardians, the PedsQL Japanese version (proxy evaluation) should be used when the patient is 14 years old or younger, and the evaluation should be done from the guardian’s perspective. (The evaluation scale is shown in Appendix 2.)

For patients

| Patient Age | | 0 year old | 1 year old | 2-4 years old | 5 years old | 6-7 years old | 8-12 years old | 13-14 years old | 15 years and older |
| --- | --- | --- | --- | --- | --- | --- | --- | --- | --- |
| QOL | EQ-5D |  |  |  |  |  |  |  | X |
|  | PedsQL |  |  |  | X** | X | X | X |  |

**: Evaluation is not mandatory.

For guardians

| Patient Age | | 0 year old | 1 year old | 2-4 years old | 5 years old | 6-7 years old | 8-12 years old | 13-14 years old | 15 years and older |
| --- | --- | --- | --- | --- | --- | --- | --- | --- | --- |
| QOL | PedsQL | X | X | X | X | X | X | X |  |

17) If periocular lesions are targeted, an ophthalmologic examination and examination should be performed the day after sclerotherapy.

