6.1.2　Diffuse lesions (if additional treatment is implemented)

In diffuse lesions, an additional treatment (one time) may be administered if the initial dose is insufficient to alleviate pain (when there is almost no change in VAS or when an exacerbation is observed) and the investigator or subinvestigator determines that an additional dose is necessary (the need for additional treatment will be determined at least 4 weeks after the initial treatment).

During the period between the initial administration and the implementation of additional treatment, observation and examination should be conducted according to the schedule in the previous section "6.1.1 Cystic and diffuse lesions (No additional treatment is needed)".

Table 6.1.2-1. Observation/examination items and implementation schedule

|  | Before treatment | | Treatment and observation period | | | | | | | | Discontinuation | |
| --- | --- | --- | --- | --- | --- | --- | --- | --- | --- | --- | --- | --- |
|  | Before administration  (Screening) | 1 day  before administration | Date of administration (first dose) | ^5)^  ... | Date of administration (additional administration) | 1 day after additional administration | 3 days after additional administration | 2 weeks after additional administration | 4 weeks after additional administration | 3 months after additional administration  (12 weeks after) | Time of discontinuance | 3 months after additional administration  (12 weeks after) |
| Tolerance (days) |  |  |  |  |  |  | ±1 | ±5 | ±5 | ±7 |  | ±7 |
| medical care category | outpatient | hospitalization | hospitalization |  | hospitalization | hospitalization | hospitalization | outpatient | outpatient | outpatient | hospitalization/  outpatient^1)^ | outpatient |
| Obtaining Consent | X ^2)^ |  |  |  |  |  |  |  |  |  |  |  |
| Eligibility assessment | X ^3)^ |  |  |  |  |  |  |  |  |  |  |  |
| Registration | X |  |  |  |  |  |  |  |  |  |  |  |
| Vital signs^4)^ |  | X |  |  |  | X | X | X | X | X | X | X |
| Body weight (usu. one's own) |  | X |  |  | X ^6)^ |  |  |  |  |  |  |  |
| Appearance^7)^ | X |  |  |  |  |  |  |  |  | X | X | X |
| Administration of an investigational drug |  |  | X ^8)^ |  | X ^8)^ |  |  |  |  |  |  |  |
| Clinical Laboratory (Blood)^9)^ | X ^10)^ |  |  |  |  | X ^11)^ |  |  |  |  | X |  |
| Urinalysis^12)^ | X ^10)^ |  |  |  |  | X ^11)^ |  |  |  |  | X |  |
| Subjective symptoms (pain)^13)^ | X ^14)^ | X ^14)^ |  |  |  | X | X | X | X | X ^14)^ | X | X ^14)^ |

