6.2.3.2　Day after administration (Tolerance ±0)

The subject should be hospitalized and will undergo the following observations and examinations will be performed.

1. Vital signs (blood pressure, pulse rate, body temperature, SpO_2_)
2. Laboratory tests (red blood cell count, hemoglobin, hematocrit, white blood cell count, platelet count, white blood cell fraction [neutrophils, lymphocytes, eosinophils, basophils, monocytes], PT, APTT, PT-INR, fibrinogen, antithrombin III, FDP, D-dimer, Na, K, Cl, Ca, IP, BUN, Cre, UA, AST, ALT, LDH, γ-GTP, T.Bil, TP, Alb, ALP, CK, TG, T-chol, HDL-chol, AMY, CRP, Glu)
3. Urinalysis (urine qualitative: sugar, protein, urobilinogen, occult blood, white blood cells, pH, specific gravity)
4. Subjective symptoms (pain)
5. Adverse event
6. Concomitant medications

6.2.3.3　3 days after administration (Tolerance ±1 day)

If there are no adverse events (abnormal liver function, abnormal renal function) associated with the administration of the investigational drug, the patient will be discharged from the hospital. The following observations and examinations will be performed prior to discharge. The acceptable range of observation days is ±1 day.

1. Vital signs (blood pressure, pulse rate, body temperature, SpO_2_ )
2. Subjective symptoms (pain)
3. Adverse event
4. Concomitant medications

6.2.3.4 　2 weeks after administration (Tolerance ±5 days)

The following observations and examinations will be performed. The acceptable range of observation days is ±5 days.

The subject will be seen as outpatients.

1. Vital signs (blood pressure, pulse rate, body temperature, SpO_2_ )
2. Subjective symptoms (pain)
3. Adverse event
4. Concomitant medications

6.2.3.5．　4 weeks after administration (Tolerance ±5 days)

The following observations and examinations will be performed. The acceptable range of observation days is ±5 days.

The subject will be seen as outpatients.

1. Vital signs (blood pressure, pulse rate, body temperature, SpO_2_)
2. Subjective symptoms (pain)
3. QOL (including ADL)
4. Adverse event
5. Concomitant medications

6.2.3.6　3 months after administration (12 weeks after administration) (Tolerance ±7 days)

The following observations and examinations will be performed. The acceptable range of observation days is ±7 days. However, for MRI imaging assessment, the acceptable range is ±14 days.

The subject will be seen as outpatients.

1. Vital signs (blood pressure, pulse rate, body temperature, SpO_2_)

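### Diffuse lesions: nothing stops an additional dose after a valid 3-month MRI, so a primary result already seen at the site can be replaced by a later one

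*Protocol*

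**What the plan says.** - **Who may be re-treated.** Protocol 4.1.11 sets a single dose, with one exception: "However, if the target lesion is a diffuse lesion, additional treatment may be performed once if necessary".
- **When and why.** Under 4.1.10, "additional treatment may be performed once within 3 months". The trigger is little or no improvement in pain on the VAS plus the investigator's view that treatment is needed. The decision may not be taken before week 4. Note 13 of Table 6.1.1-1 repeats the upper limit: "an additional treatment (one time) may be administered within 3 months".
- **When the primary MRI is valid.** Table 6.1.1-1 and section 6.2.3.6 equate 3 months with 12 weeks. Note 15 of the table adds: "For MRI imaging only, the acceptable range after 3 months of administration is ±14 days". Section 6.2.3.6 says the same: "However, for MRI imaging assessment, the acceptable range is ±14 days".
- **What applies until re-treatment.** For the time between the two doses, 6.1.2 says "observation and examination should be conducted according to the schedule in the previous section", which is the single-dose schedule. That schedule contains the 3-month MRI.
- **Which result counts.** Section 5.1: "If additional treatment (one time) is given, the results are evaluated 3 months after the additional dose", compared with the state before the first dose. Volume is calculated by a Central Judgment Committee independent of the investigators.

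No section requires the additional dose to come before the 3-month MRI, and none forbids it afterwards.

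**The concern.** The number of doses determines which MRI is the primary evaluation, and the number of doses can still change after the first valid MRI exists. The trial is open-label, part of the trigger is the investigator's judgement, and no section keeps the site from seeing its own images. Among subjects whose pain has hardly improved, a poor scan could tip the judgement towards a second dose and a good scan could tip it away. Observed non-responders would then get a second reading that responders do not need.

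The diffuse cohort is tested against a fixed 20% response rate with no control arm, so selection of this kind would not cancel against a comparator. At stake is the credibility of a primary result that could be overwritten after it was seen.

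**Working it through.** **1. The protocol's own sample size (8.6.2, cystic cohort).** Exact binomial, null 20%, expected 50%, one-sided 2.5%. With n = 19, 8 responders are needed; P(X ≥ 8 | 19, 0.2) = 0.0233 and power at 50% is 0.820. With n = 18 the power is 0.760. The stated 19 is reproduced.

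**2. The rule for the diffuse cohort.** The target is 22, set by feasibility; all 22 are taken here as evaluable. P(X ≥ 8 | 22, 0.2) = 0.0561 and P(X ≥ 9 | 22, 0.2) = 0.0201, so 9 responders are needed. Power at 50% is 0.857.

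**3. The windows.**
- Nominal 3-month MRI: 12 × 7 = day 84. Window: 84 − 14 = day 70 to 84 + 14 = day 98.
- Last day for the additional dose: day 84 at 12 weeks (about day 90 to 92 if calendar months were meant).
- Overlap: days 70 to 84. After an MRI on day 70, a dose on days 71 to 84 is permitted.
- If the 3-month pain visit (±7 days) prompts the dose, the overlap starts on 84 − 7 = day 77.
- The replacing MRI falls on days 71 + 70 = 141 to 71 + 98 = 169 for a dose on day 71, and on days 84 + 70 = 154 to 84 + 98 = 182 for a dose on day 84.

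**4. Illustration of size.** The protocol gives neither the shares re-treated after the MRI nor the agreement between repeat MRIs. These are assumptions:
- true first-MRI response rate 20%, and no effect of the second dose;
- f = share of first-MRI failures re-treated after the scan, g = the same share among responders;
- a = chance that a first-MRI responder reads as a responder again, c = chance that a failure reads as a responder.

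Keeping 20% responders overall at the second reading requires 0.2a + 0.8c = 0.2, so c = 0.25(1 − a). The rate that enters the test is

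p = 0.2(1 − g) + 0.2·g·a + 0.8·f·c = 0.2 + 0.2(1 − a)(f − g).

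The chance of at least 9 responders in 22:

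| Repeat agreement a | f = 5%, g = 2.5% | f = 10%, g = 5% | f = 25%, g = 10% | f − g at which 2.5% is reached |
| --- | --- | --- | --- | --- |
| 100% | 2.0% | 2.0% | 2.0% | never |
| 80% | 2.1% | 2.1% | 2.4% | about 18 points |
| 50% | 2.2% | 2.3% | 3.1% | about 7 points |
| 20% (chance only) | 2.3% | 2.6% | 4.0% | about 4.4 points |

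For the f = 25%, g = 10% column, f − g = 0.15 and p = 0.200, 0.206, 0.215 and 0.224 from top to bottom. In expected numbers that column is 22 × 0.8 × 0.25 = 4.4 failures and 22 × 0.2 × 0.10 = 0.44 responders re-treated after the scan. The last column of the table follows from P(X ≥ 9 | 22, p) = 0.025 at p = 0.2071, so f − g = 0.0071 / [0.2(1 − a)].

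If f = g, then p = 0.2 and the chance stays at 2.0% whatever the agreement.

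**The case against.** **The endpoint is defined.** Section 5.1 fixes which MRI counts once the number of doses is known, and for response after up to two doses the exact test has size 2.0%. This stands. A reader might take the 4.0% above as an inflated type I error of the planned test. The protocol does not support that: p = 0.224 exceeds 20% on the endpoint as defined, and the excess is an error only against a first-MRI endpoint that 5.1 does not use for re-treated subjects.

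**The trigger is pain, not volume.** This also stands. A reader might infer bias even if nobody acts on the scan, because 5.1.1 says that "many literature studies have shown that patients with lesion reduction also experience improvement in pain", so a pain trigger would pick out volume failures. But a dose given purely for pain leads to the same later evaluation whether or not a first MRI was taken, so the order adds nothing. Harm needs the scan itself to influence the judgement of need.

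**Low repeat agreement is implausible.** Two volume readings of one lesion against one baseline should agree well, and at 80% agreement every case shown stays below 2.5%. The 4.0% is an extreme.

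**The overlap is narrow.** Note 13 is attached to the 4-week pain assessment, the natural decision point, and no pain visit is scheduled between it and the 3-month visit. An early MRI, a later decision, admission and sclerotherapy must all fit into about two weeks. This makes the sequence uncommon but does not exclude it.

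**Central reading.** The independent committee protects the volume measurement. It does not govern which scan becomes the primary one.

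**Conclusion.** The gap is real and minor. The protocol's own windows permit a valid 3-month MRI from day 70 followed by an additional dose up to day 84, and 5.1 then replaces that MRI. The two-dose strategy is not at fault, and neither is a dose prompted by pain alone. The residual risk is limited to diffuse-lesion subjects who have little pain improvement, who were scanned before the decision, and whose scan influenced it.

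The effect is probably small and cannot be quantified from the protocol. With 25% of failures and 10% of responders re-treated because of what was seen, the chance of success at a 20% first-MRI rate runs from 2.0% with full repeat agreement to 4.0% with none beyond chance, and is about 2.4% at 80%. Those shares and agreement levels are assumptions. If the second dose works, some of the added responders are genuine. The point justifies a cheap clarification; it does not show that the planned analysis is invalid.

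**What to change.** In 4.1.10 and in note 13 of Table 6.1.1-1, state that additional treatment must be decided and given before the 3-month MRI is taken, and that no additional study dose is given after that MRI. No fixed earlier cut-off day is needed: the decision is already open from week 4 (day 28), six weeks before the MRI window opens on day 70. The rule in 5.1 and the test of 9 responders in 22 stay as they are.

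The cost is a protocol amendment with IRB review at each site, and the loss of in-trial re-treatment for the few subjects whose persistent pain is acted on only after the 3-month MRI. No procedure is added. A sensitivity analysis that scores any subject re-treated out of order on the first MRI can be left to the SAP.

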| Efficacy endpoints | The efficacy evaluations below refer to the case of single administration. If additional treatment is given, evaluation is conducted 3 months after additional administration (1 month after additional administration for number 2 in "2.2 Other secondary endpoints" below) compared to that before the first administration.   1. Primary Endpoint   20% or more reduction in volume of venous malformations at the time of 3 months after intervention   1. Secondary endpoint   2.1 Significant secondary endpoint  Improvement in symptoms such as pain originated from venous malformations at the time of 3 months after intervention  2.2 Other secondary endpoints  1) Reduction rate in volume of venous malformations at the time of 3 months after intervention  2) Improvement in symptoms such as pain originated from venous malformations at the time of 1 months (4 weeks) after intervention  3) Improvement of QOL (ADL) at the time of 3 months after intervention   1. Other endpoints   Change in appearance at the time of 3 months after intervention; significant improvement, moderate improvement, no change and exacerbation. |
| Safety endpoints | Adverse events, side effects, laboratory values |

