8.2.2.2.2　Analysis for other secondary endpoints

(1) The median percent reduction from baseline (prior to administration) and its 95% confidence interval for the reduction rate (volume) of the target lesion at 3 months after sclerotherapy will be estimated. Also, a Wilcoxon signed-rank test is performed under a null hypothesis of "The median reduction rate (volume) of the target lesion at 3 months after sclerotherapy is less than or equal to zero. The significance level is set at 2.5% one-sided.

(2) The median -1-fold change from baseline (prior to administration) to 1 month post sclerotherapy and its 95% confidence interval for the symptom (pain) score associated with the target lesion at 1 month (4 weeks) post sclerotherapy will be estimated. Also, a Wilcoxon signed-rank test is performed under a null hypothesis of "the median -1-fold change from baseline to one month after sclerotherapy in the population is less than or equal to zero." The significance level is set at 2.5% one-sided.

(3) The median change from baseline (prior to administration) to 3 months after sclerotherapy and its 95% confidence interval for the QOL score will be estimated. A Wilcoxon signed-rank test is performed under a null hypothesis of "the median change from baseline to 3 months after sclerotherapy for the population is less than or equal to zero." The significance level is set at 2.5% one-sided.

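### In the diffuse cohort, the 1-month pain endpoint lets a poor 4-week reading be superseded after retreatment while good readings stand, so its one-sided 2.5% test does not hold its level

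*Protocol*

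**What the plan says.** Three parts of the protocol combine here.

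- **Trigger for the additional dose.** Section 4.1.10, for diffuse lesions only, allows one further session when "there is little improvement in symptoms such as pain after 4 weeks from the initial treatment (when there is almost no change in VAS" or pain has worsened) and the investigator considers it necessary. The decision comes at least 4 weeks after the first session, and the dose is given within 3 months. In Table 6.1.1-1 the same rule is a footnote on the 4-week pain assessment itself: "if there is lack of improvement in pain after 4 weeks from the initial treatment and the investigator or subinvestigator determines" that it is needed.
- **Reading used for the endpoint.** Pain at 1 month (4 weeks) is item 2 of section 5.1.2.2. When an additional dose has been given, section 5.1 states that "the results are evaluated 3 months after the additional dose (1 month after the additional dose for" that item), "compared with the results before the first dose". The synopsis repeats the rule: "1 month after additional administration for number 2 in" its list of other secondary endpoints.
- **Test.** Section 8.2.2.2.2(2) takes "The median -1-fold change from baseline (prior to administration) to 1 month post sclerotherapy" and applies a Wilcoxon signed-rank test against a median of zero or less at one-sided 2.5%. Section 8 analyses the diffuse cohort on its own for all endpoints.

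The reading 4 weeks after the first dose is not lost. Section 6.1.2 says: "During the period between the initial administration and the implementation of additional treatment, observation and examination should be conducted according to the schedule" of section 6.1.1, which includes that visit.

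**The concern.** Whether a subject's 1-month value is replaced depends on the pain response that the endpoint measures. A subject who has improved at 4 weeks keeps that value; one who has not may be read again later. Part of a poor reading is usually chance variation, so a second reading tends to be better even when neither dose does anything. The signed-rank test assumes that, under no change, differences from baseline scatter symmetrically about zero. Selective replacement breaks that symmetry in the favourable direction.

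The endpoint also mixes two quantities. One-dose subjects contribute a value 4 weeks after their only dose. Retreated subjects contribute a value after two doses, at the earliest about 4 + 4 = 8 weeks and at the latest about 12 + 4 = 16 weeks after the first. Both carry the 1-month label.

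At stake is a formal hypothesis test on pain in the cohort where section 5.1.2.1 calls pain improvement especially important, in an open-label trial that section 2.1 justifies by the subjective endpoints of earlier studies.

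**Working it through.** The protocol gives no figure for this test. Its only sample-size figure, 19 for the cystic cohort, does reproduce: an exact binomial test of 20% against 50% with 8 or more responders has size 0.0233 and power 0.8204, while 18 subjects give power 0.7597. It does not bear on this point.

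**Inputs from the protocol:** 22 diffuse subjects including dropouts (section 8.6.2); one-sided 2.5% signed-rank test; replacement rule and baseline as in section 5.1.

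**Assumptions, because the protocol is silent:** the VAS cut-off, the share of eligible subjects retreated, and the correlation between readings. VAS is treated as continuous and normal.

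**Model.** Let e0, e1 and e2 be pain before the first dose, 4 weeks after it, and 1 month after the additional dose. Let D1 = e0 - e1 and D2 = e0 - e2, so positive means improvement. The analysed value is A = D2 if the subject is retreated, otherwise D1. Retreatment requires D1 <= 0 (no improvement). With no effect, half the cohort is eligible, so retreating a share q of those eligible retreats q/2 of the cohort.

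**Direction.**

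1. With independent readings, E[D2 | D1] = 0.5 D1. If all eligible subjects are retreated, E[A] = E[D1; D1>0] + 0.5 E[D1; D1<=0]. Since E[D1] = 0, this equals 0.5 E[D1; D1>0].
2. With D1 scaled to SD 1, E[D1; D1>0] = 0.399, so E[A] = 0.5 x 0.399 = 0.20 SD. Simulation gives 0.198.
3. With serial correlation (neighbouring readings r, outer pair r squared), E[D2 | D1] = D1 (1 + r)/2. At r = 0.8 the factor is 0.9, so E[A] = 0.1 E[D1; D1>0]. With VAS SD 15 mm, the SD of D1 is 15 x sqrt(2 x 0.2) = 9.5 mm, and E[A] = 0.1 x 0.399 x 9.5 = 0.4 mm.
4. The test responds to signs and ranks more than to the mean. The probability that A is positive is 0.5 + arccos(k)/(2 pi), where k = sqrt(1 + r)/2 is the correlation of D1 and D2. For r = 0, k = 0.5 and the probability is 0.5 + 1/6 = 0.667. For r = 0.8, k = 0.671 and it is 0.5 + 0.133 = 0.633. Without replacement it is 0.5.

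**Size of the test.** At n = 22 the exact one-sided critical value is W+ >= 188, with attainable size 0.0231. Simulated rejection rates with no effect of either dose:

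| Share of cohort retreated | Independent readings | r = 0.5 | r = 0.8 |
|---|---|---|---|
| None, or first 4-week value used for all | 2.3% | 2.3% | 2.3% |
| 12.5% | 4.4% | 3.6% | 3.4% |
| 25% | 7.8% | 5.6% | 4.6% |
| 50% | 19.7% | 11.1% | 7.9% |

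**Sensitivity.** With 5% of the cohort retreated the rate is 3.1% (independent) or 2.7% (r = 0.8). With a looser cut-off (improvement up to 0.25 SD) and independent readings it is 4.1%, 7.0%, 10.7% and 15.5% for 15%, 30%, 45% and 60% retreated. At n = 19 the independent-readings range over both cut-offs is 4.2% to 18.5%.

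**The case against.** The strongest defence is that the rule is a declared strategy: retreated subjects are judged after their last session, as for the 3-month endpoints and the observation period. The effect of a course of up to two sessions is a legitimate target. That stands as a choice of question, but it does not validate this test. At 1 month the reading named by the endpoint has already been taken, and a poor one may be superseded. The 3-month endpoints do not work that way: the additional dose falls within the 3 months, so no 3-month reading is taken and then replaced.

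Section 3.1 says that these lesions basically worsen without treatment, which would pull later readings down. With independent readings, SD 15 mm and an assumed worsening of 2 mm then 4 mm, rejection is 1.4%, 2.7% and 6.5% at about 13%, 27% and 54% retreated; with 3 mm then 6 mm it is 0.9%, 1.3% and 3.5%. This reduces the practical size. But worsening lies inside the null hypothesis, and a test must hold its level at the no-change boundary as well.

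A reader might infer that false-positive rates of 10-20% are to be expected. The protocol does not support that: such rates need a large part of the cohort retreated and weakly correlated readings, while a second session also requires investigator judgement and a hospital stay. A reader might also infer that the 4-week value alone decides retreatment, or that it is thrown away. Neither is so. The decision may come later than week 4, and section 6.1.2 keeps the reading, so a supplementary analysis of it remains possible. That would help, but the test fixed by the protocol would still be the inflated one.

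**Conclusion.** The point holds, at the level of something that should be fixed. Following sections 5.1 and 8.2.2.2.2(2) as written applies a test against zero to values selected by outcome. At the no-change boundary its one-sided level rises from 2.3% to about 3-4%, 5-8% or 8-20% when 12.5%, 25% or 50% of the diffuse cohort is retreated. The lower ends assume serial correlation of 0.8 and the upper ends independent readings; all assume 22 subjects and a cut-off of no improvement. The excess is nil if nobody is retreated and smaller if untreated pain worsens over time.

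The scope is one non-key secondary endpoint in one cohort. A reader might extend it to the trial's main efficacy conclusions. The documents do not support that: cystic lesions cannot be retreated, and neither the primary volume endpoint nor the 3-month pain endpoint is affected by this mechanism. Nor does it show any fault in the retreatment rule itself.

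**What to change.** In the synopsis (efficacy endpoints and main statistical methods), section 5.1 and section 8.2.2.2.2(2), define the tested 1-month pain endpoint for every subject as the reading 4 weeks after the first administration, against the value before it. Report the reading 4 weeks after the additional administration separately and descriptively for retreated subjects. In the simulations this returns the test to 2.2-2.4% at n = 22. The 3-month endpoints and the retreatment rule stay as they are.

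No new visit or measurement is needed. The cost is a protocol amendment, which under section 10 needs agreement among the investigators and IRB review at each site; it should be in place before the data are fixed. The endpoint would then describe the first session only, and the 1-month result in diffuse lesions may look less favourable.
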